#### Outcomes

The primary trial outcome of interest is the proportion of patients with TB successfully treated (final value), defined according to the World Health Organization criteria [21] as the total number of patients cured and completing treatment. Secondary trial outcomes include the proportion of default cases (treatment interrupted for at least 2 consecutive months) and proportion of successes among cases with HIV coinfection. All outcomes will be assessed for 1 year following completion of LHW on-site peer-led training.

#### Sample size calculation

Although 109 HCs are available for participation in the 4 study districts, we expect that a small number do not routinely provide TB care. In addition, on the basis of our experience in the preliminary study, where several clusters were lost because of staff shortages necessitating transfer of TB cases or failure of HCs to accrue eligible TB cases in small, remote HCs, we have estimated the sample size for the present study conservatively as follows. With an alpha of 0.05, a power of 0.80, a baseline successful treatment completion of 0.80 at 1 year, an intraclass correlation coefficient of 0.1 based on our pilot study data, and an estimated 100 clusters (HCs that provide TB care), a minimum of 6 patients are required per cluster to detect a clinically significant 0.10 increase in the proportion of successful treatment completion.

#### Analysis plan

Summary statistics, including measures of central tendency and range, will be calculated and presented for each district, including number of HCs included, number of individuals receiving the intervention, number of LHWs trained at each site, baseline characteristics (proportion of pulmonary and nonpulmonary TB cases), proportion with TB-HIV coinfection, and TB outcomes across the trial arms by district.

The primary analysis will use multilevel modeling to compare proportion of treatment successes among the control and intervention groups, with analysis adjusted for correlation due to clustering and stratification. Multilevel modeling will also allow us to examine similarities and differences between and within districts (strata) and healthcare centers (clusters) in outcomes and for planned subgroup analysis. Analysis will be conducted on an as-randomized basis and performed using R statistical software.

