### Cluster RCT

#### Setting, participants, and randomization

Dignitas International (DI) works closely with the Malawi Ministry of Health (MOH) to support health system-strengthening and to build capacity among healthcare workers to improve clinical care and outcomes. This project will include all health centers (HCs) providing TB care among the 109 HCs in 4 of the 6 districts in which DI operates, excluding the district included in our preliminary study and an additional district that declined to participate. As TB care is provided at HCs on a rotating basis, patients receive care from several LHWs during treatment. Given this system of care, a cluster RCT (with allocation at the HC level) was chosen to prevent contamination. HCs will be randomly allocated in a 1:1 ratio based on a superiority framework using a computer-generated random number list prepared by a study team member without knowledge of the districts or HCs themselves, and they will be allocated by a second study team member. Once generated, the randomization information will be provided to a second study team member who will assign HCs as intervention or control sites by applying the random number list to the HC list provided by the district health offices. Randomization will be stratified by district, HC funding (MOH-funded vs non-MOH-funded), and HC designation as a priority site for support and mentorship. These stratification variables are chosen to address district-level variations in operationalization of TB policy and the potential for LHWs at priority sites to receive additional clinical training relevant to TB care.

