#### Data collection

A digital copy will be made of TB registers of all participating districts at the end of the 1-year trial period. Data will be double-entered and verified by a data manager.

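### The primary model names only clustering and the strata; pre-specifying TB type and HIV status at treatment start would add modest precision at almost no cost

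*Protocol article*

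**What the plan says.** The Analysis plan of the cluster trial compares treatment success between arms by multilevel modelling, "with analysis adjusted for correlation due to clustering and stratification". The section on setting, participants and randomization defines the strata: "Randomization will be stratified by district, HC funding (MOH-funded vs non-MOH-funded), and HC designation as a priority site for support and mentorship". All three are features of the health centre (HC) or its district.

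The same Analysis plan lists, for descriptive summary, "baseline characteristics (proportion of pulmonary and nonpulmonary TB cases), proportion with TB-HIV coinfection, and TB outcomes across the trial arms by district". The Outcomes section adds a secondary outcome, the "proportion of successes among cases with HIV coinfection". TB type and HIV coinfection must therefore both be extracted, but neither is named in the primary model.

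On the data source, the Data collection section says: "A digital copy will be made of TB registers of all participating districts at the end of the 1-year trial period". The Outcomes section says: "All outcomes will be assessed for 1 year following completion of LHW on-site peer-led training". Neither sentence says that the copy covers a period before training.

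**The concern.** Treatment success plausibly depends on HIV coinfection and TB type, and HCs plausibly differ persistently in performance. A model that leaves these out stays valid, but it is less precise than it could be and leaves chance differences in case mix uncorrected.

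The point has some weight here for two reasons. At the stated minimum cluster size the design only just reaches its power target. Also, allocation is by HC and patients register afterwards, so case mix is balanced only through the randomization of about 100 HCs, and none of the strata captures HIV status or TB type. At stake are a few points of power and a small possible shift in the estimate, not the validity of the trial.

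**Working it through.** **Inputs from the Sample size calculation section:** control success 0.80, target increase 0.10, alpha 0.05, power 0.80, intraclass correlation (ICC) 0.1, 100 HCs, minimum 6 patients per HC. Allocation is 1:1, so 50 HCs per arm. Sidedness is not stated; two-sided is assumed.

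**Step 1. Reproduce the plan's figure.** Two proportions, pooled variance, no continuity correction:

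n = [1.960·√(2·0.85·0.15) + 0.8416·√(0.80·0.20 + 0.90·0.10)]² / 0.10² = [0.990 + 0.421]² / 0.01 ≈ 199 per arm.

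With design effect 1 + (m − 1)·0.1 and 50 HCs per arm, m = 199·0.9 / (50 − 199·0.1) = 179.1 / 30.1 = 5.95, so 6. At m = 6 the design effect is 1.5: 199·1.5 = 298.5 patients needed per arm, 300 available, power 0.802. The stated figure is right and assumes no covariate adjustment.

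**Step 2. Split the variance of an HC mean at m = 6.** In units of total variance: between-HC 0.1, within-HC 0.9/6 = 0.15, total 0.25. The between-HC share is 0.1/0.25 = 40%; the other 60% is patient sampling.

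**Step 3. Add HIV status and TB type.** The documents give no association with outcome, so the explained shares are assumed.

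| Within-HC variance explained | Between-HC variance explained | Variance ratio | Power |
|---|---|---|---|
| 2% | 0% | (0.100 + 0.147)/0.25 = 0.988 | 0.807 |
| 5% | 0% | (0.100 + 0.1425)/0.25 = 0.970 | 0.814 |
| 2% | 10% | (0.090 + 0.147)/0.25 = 0.948 | 0.823 |
| 5% | 20% | (0.080 + 0.1425)/0.25 = 0.890 | 0.846 |

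Against 0.802 this is a gain of about 0.5 to 4 points.

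**Step 4. Add the HC's pre-training success proportion.** The reliability of an HC proportion is 0.1m / (1 + 0.1(m − 1)): 0.6/1.5 = 0.40 at m = 6 and 2/2.9 = 0.69 at m = 20. With an assumed between-period correlation c of true HC rates, r = c·√(reliability before × reliability in trial), and the variance ratio is 1 − r². Trial cluster size is held at 6.

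| Earlier patients per HC | c | r | 1 − r² | Power |
|---|---|---|---|---|
| 6 | 0.5 | 0.20 | 0.960 | 0.818 |
| 6 | 0.8 | 0.32 | 0.898 | 0.843 |
| 6 | 1.0 | 0.40 | 0.840 | 0.866 |
| 20 | 0.5 | 0.263 | 0.931 | 0.829 |
| 20 | 1.0 | 0.525 | 0.724 | 0.911 |

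With 6 earlier patients per HC the gain is about 2 to 6 points. The 11 points in the last row need 20 earlier patients and perfectly stable HC performance.

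**Step 5. Size of a case-mix shift.** Assume 50% HIV prevalence, with an ICC for HIV status of 0.01 to 0.10 and 300 patients per arm. The standard error of the chance difference in prevalence is √[2·0.25·(1 + 5·ICC)/300] = 0.042 to 0.050. A 10-point imbalance, about two standard errors, combined with an assumed 10-point outcome gap by HIV status shifts the effect by 0.10·0.10 = 0.01, that is, 1 point against a target of 10.

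**Limits.** These are linear-scale approximations. The strata may already absorb some between-HC variation, which would shrink the gains. The gains in Steps 3 and 4 may overlap and should not be added.

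**The case against.** The strongest reply is that nothing here is an error. A multilevel model that respects clustering and strata is a sound primary analysis, no other statement contradicts it, and the sample size holds without covariates. A fuller covariate list could also sit in an analysis plan that is not shown. The first part stands in full. The second stands in part: the article does not say that no other covariate will be used, but it does state a specific adjustment set. Adding to it would change the published primary analysis and should be done openly before outcomes are seen.

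A reader might infer four stronger claims, which the documents do not support:

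- **That the copied registers already hold each HC's earlier success proportion.** This is plausible for routine registers, but the period covered is not stated and outcomes are confined to the year after training.
- **That between-HC variation dominates the standard error.** At 6 patients per HC it makes up 40% of the variance of an HC mean.
- **That large gains are within reach.** With 20 patients per HC in both periods and c of 0.5 to 0.8, r is about 0.34 to 0.55 and the variance falls by 12 to 30%. But at that size the unadjusted trial has an effective sample of 1,000/2.9 = 345 per arm and power of about 0.96. Six is also a minimum, not the expected cluster size.
- **That case mix is unbalanced because patients were not themselves randomized.** Randomizing about 100 HCs balances it in expectation; only chance imbalance remains.

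One objection narrows the remedy. Patients register after allocation, and Table 1 lists the interaction of TB and HIV among the topics taught. Recording of HIV status, above all how often it is unknown, could therefore differ by arm. Adjusting for a variable that the intervention has changed can introduce bias. This limits the covariates to those fixed at treatment start and calls for a check on HIV recording.

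**Conclusion.** The point holds as a missed efficiency, not as a fault in the planned analysis. The primary model names no prognostic covariate beyond the strata, while two candidates will be in the dataset anyway. From a reference of 0.80, HIV status and TB type would add about 0.5 to 4 power points if they explain 2 to 5% of within-HC and 0 to 20% of between-HC variance. Pre-training HC success would add about 2 to 6 points at 6 patients per HC and a between-period correlation of 0.5 to 1.0, provided that earlier register pages can be extracted. None of these explained shares or correlations comes from the documents. Protection against chance imbalance is worth about 1 point of effect in the illustrated case. The change is worth making because it costs so little.

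**What to change.** Before outcome data are seen, amend the Analysis plan as follows.

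1. Include in the primary model pulmonary versus nonpulmonary TB and HIV status (positive, negative, unknown), both as recorded at treatment start. This needs no new data collection.
2. Fix a rule for HIV status in advance. Tabulate its recording by arm, including the unknown category, with outcome columns withheld. If recording differs by arm, move HIV status to a sensitivity analysis and keep TB type in the primary model.
3. State the period that the register copy covers. If earlier Ministry of Health register pages can be extracted, add each HC's success proportion from the last full cohort before training. Allocation cannot affect it. It needs two counts per HC (patients registered, patients successful), about 200 counts for 100 HCs. If the pages cannot be extracted, leave it out.
4. Report the adjusted effect as a standardized risk difference with a confidence interval that accounts for clustering, so that it is on the scale of the 0.10 target. Report the strata-only model as a sensitivity analysis.

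The sample size needs no change. The remaining cost is a short protocol amendment and some extra programming.

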### Process evaluation

#### Setting and participants

Interview participants will include LHWs who have received the intervention and patients and/or guardians who begin TB treatment on or after the trial start date and who are followed at a participating HC.

#### Inclusion and exclusion criteria

LHWs who have completed the educational outreach training and patients with TB of participating HCs who begin TB treatment during the trial period presenting for TB care on days the study research assistant (RA) is collecting data will be eligible for participation in the qualitative study. Exclusion criteria for interview participants include patients with TB who are younger than 18 years of age and unaccompanied by a parent or guardian, patients and/or guardians or LHWs who are unwilling or unable to give informed consent, patients who are not usually treated at the participating HC, and patients deemed by the local healthcare team to be too ill to participate.

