#### KT intervention

The current strategy builds on our earlier work, in which we identified a gap in LHW TB knowledge and job-specific training [9–11]. The multifaceted KT strategy will employ peer trainer-led educational outreach, a point-of-care reminder tool, and a peer mentoring network, chosen on the basis of evidence for the effectiveness of this approach with midlevel healthcare workers in South Africa [12–14], mapping of barriers to implementation identified through our formative qualitative study [10], and experience with and feedback from our prior studies [9, 11]. Improved patient TB knowledge and positive patient-provider interactions, two common barriers to adherence [15–18], are targeted through improved LHW skills in patient education and adherence counseling. Although evidence for communities of practice is poor [19], we include a peer mentorship network based on previous feedback from peer trainers to evaluate its potential role and cost implications. See Table 1 and Figs. 2 and 3 for detailed descriptions of the intervention and the point-of-care tool. The full manual is available upon request from the corresponding author.

**Table 1 Tab1:** Description of the intervention

Details of intervention	Intervention group
Rationale/goals	The intervention was designed to target a recognized gap in TB care provided by LHWs by targeting two common barriers to adherence—patient disease understanding and patient-provider relationship—through improved LHW TB knowledge and skills in patient education and counseling.
Materials	The educational outreach component will use a combination of didactic and interactive techniques, including small- and large-group case-based discussions, role-playing to efficiently convey TB disease and treatment knowledge and patient education and counseling skills as well as to allow practice with the point-of-care tool and exchange of ideas between LHWs. Topics to be covered include TB transmission and treatment, risk factors for and consequences of poor adherence, the interaction of TB and HIV, treatment side effects and their management, and approaches to preventing and addressing nonadherence while maintaining a positive patient-provider relationship.

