#### Participant recruitment and informed consent

Two to four participants from each group (LHWs and patients) will be selected in each data collection period from each district and a maximum of two from any one HC. LHWs will be selected for interviews using mixed purposive sampling. A list of trained LHWs compiled by the peer trainers will provide the initial sampling frame. LHWs will be selected from among those on the list to represent the range of LHW characteristics in terms of gender, age, years of experience, and HC characteristics (rural vs urban). Three LHWs chosen to reflect the range of responses (positive to negative) in the first round of interviews will be selected to be interviewed at both study onset and conclusion. The study, SC, or RA will be introduced to the general LHWs by the peer trainers. LHWs will then be approached in person (or by phone if the selected LHW is not present on site at the time of the HC visit) by the SC or RA, who will use a recruitment script.

Convenience sampling will be used to select patients and/or guardians for interviews. Patients will be selected to represent the range of characteristics in terms of age, gender, and TB characteristics (new vs recurrent, pulmonary vs nonpulmonary). The SC or RA will attend HCs on days identified by HC staff as typically busy. The SC or RA will be introduced to patients by the LHWs working in the HC during HC visits. After being introduced, the SC or RA will approach patients in person, using a recruitment script.

Written informed consent will be obtained in person by the SC or RA prior to beginning the interview. In order to ensure participant understanding, in addition to providing the consent form in Chichewa, the SC or RA will read the consent form out loud. Participants will then be given an opportunity to read the consent form and to have any questions they may have answered by the study team. Once all questions are answered to the participants’ satisfaction, the participants will be asked if they wish to participate; if they agree, the form will be signed and witnessed. For patients under 18 years of age, consent will be obtained from the child’s parent or guardian using the same process, and assent will be obtained for children old enough to participate in interviews after parental consent has been obtained.

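### Patient interviews reach only people in care on a visit day, and treatment interruption is not a sampling characteristic

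*Protocol article*

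**What the plan says.** In the process evaluation, Inclusion and exclusion criteria gives the rule for patients who started treatment in the trial period: those "presenting for TB care on days the study research assistant (RA) is collecting data will be eligible for participation in the qualitative study". Setting and participants also requires that they be under follow-up at a participating health center.

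Participant recruitment and informed consent says how patients are found and chosen:

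- Method: "Convenience sampling will be used to select patients and/or guardians for interviews".
- Characteristics: "Patients will be selected to represent the range of characteristics in terms of age, gender, and TB characteristics (new vs recurrent, pulmonary vs nonpulmonary").
- Place and time: "The SC or RA will attend HCs on days identified by HC staff as typically busy".
- Approach: the center's own lay health workers (LHWs) make the introduction. "After being introduced, the SC or RA will approach patients in person, using a recruitment script".

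For LHWs, the same section uses purposive sampling and lets the team make contact "or by phone if the selected LHW is not present on site at the time of the HC visit". It also picks three LHWs for re-interview so that views from positive to negative are covered.

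In the trial part, Table 1 describes the intervention as "targeting two common barriers to adherence—patient disease understanding and patient-provider relationship", and Outcomes states: "Secondary trial outcomes include the proportion of default cases (treatment interrupted for at least 2 consecutive months"). The process evaluation has its own Outcomes section, which covers what helps or hinders implementation, scale-up and sustainability, and possible improvements to the program.

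**The concern.** The intervention works on adherence through the patient's understanding and the relationship with the provider. Patient interviews are the only source in which patients speak for themselves about either. Yet the entry rule for those interviews is attendance, which is close to the behavior the intervention tries to change. A patient who has stopped coming cannot be interviewed at that time, and nothing in the sampling looks for patients who stopped and returned.

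At stake is what the patient interviews can say about barriers and program improvements. If counseling or the relationship broke down for some patients, those still away are the ones the rule leaves out. Introduction by the LHWs whose care is under discussion may push accounts further in the same direction. Advice on scale-up could then rest on patient views that are too favorable.

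**Working it through.** This is mainly a reading of the rules side by side. The arithmetic only sets the scale.

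**1. The plan's own interview total.** Sample size calculation (process evaluation) gives 10–15 people per group, two groups and two time points. 10 × 2 × 2 = 40 and 15 × 2 × 2 = 60, which reproduces the stated 40–60. Patients are one of the two groups: 10 × 2 = 20 to 15 × 2 = 30 interviews.

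**2. Who can be among those 20–30.** The trial defines default as an interruption of at least two consecutive months.

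- *Still out of care on visit days:* not presenting, so not eligible. Recruitment offers no other route; the phone option is written for LHWs only. Guardians do not open one, because eligibility still turns on the patient presenting.
- *Interrupted and returned:* presenting, so eligible.
- *Shorter gaps or missed doses, still attending:* eligible.

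The rule therefore excludes only the first group.

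**3. Whether the sampling looks for the second group.** The listed characteristics are age, gender, new or recurrent disease, and pulmonary or nonpulmonary disease. None records whether the present course was interrupted. With convenience sampling, a returned patient enters only by chance.

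**4. Whether the gap can be sized.** The protocol gives a baseline success of 0.80 (trial Sample size calculation), so 1 − 0.80 = 20% do not succeed. Background gives completion of 58–70% in the earlier study, so 1 − 0.70 = 30% to 1 − 0.58 = 42% did not complete. Both shares include deaths and other outcomes as well as default. The second comes from Zomba District, where the earlier work was done, and this trial excludes the pilot district. Neither is a default rate, and the protocol gives none.

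**5. Timing of the two rounds.** Data collection (process evaluation) places round 1 in the first 3 months after training and round 2 in the last 3 months of the 1-year trial. Assume that the trial period starts when training ends, which the protocol does not state exactly. To have completed a two-month interruption by the end of round 1, a patient must have started and stopped treatment by month 3 − 2 = 1. By the start of round 2 (month 12 − 3 = 9), the limit is month 9 − 2 = 7. An earlier start would lengthen both windows, but round 2 stays much the better place to find such patients.

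**6. Effect on trial results.** Data collection (cluster RCT) takes outcomes from TB registers. Who is interviewed does not enter the success or default proportions.

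**The case against.** The strongest defense has four parts.

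- **Task.** The process evaluation is not asked to explain default. Its stated outcomes are about implementation, scale-up, sustainability and program improvement. This stands, and it limits the point. A reader might infer that the interviews must account for a null effect on success or default; the protocol does not give them that job. Barriers and program improvements are in scope, however, and there the gap matters.
- **Other sources.** LHW interviews, training logs and meeting notes are combined with the patient interviews, and LHWs can describe nonadherence. This stands in part: their account is second-hand.
- **Overreading.** A reader might infer that patients who stopped treatment are never heard, or that every interviewee is someone for whom adherence held. The criteria do not support this, since returned interrupters and patients with shorter gaps are eligible.
- **Ordinary practice.** Convenience sampling is declared openly, and a qualitative component of 20–30 patients commonly has this limit. This is fair, and it is why the point is a cheap improvement and not a flaw in the trial.

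A full tracing scheme would also meet real obstacles. Data management limits identifiers in the digitized registers to checking double entry, and those copies are made only at the end of the trial. Setting and participants would still require follow-up at the center. Consent is written and given in person, and nothing shows that patient phone numbers are held.

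**Conclusion.** The point holds in a limited form. A patient who is out of care when the research assistant visits is not eligible for interview, and interruption history is not sampled for, so returned interrupters appear only by chance. All 20–30 patient accounts will come from people attending care, and they may be too favorable about barriers and program improvements. That direction is plausible but not demonstrated.

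The size is unknown. It would be tempting to read 20% or 30–42% as the share of patients left out, but those figures are non-success and non-completion from all causes, and the protocol states no default rate. The randomized comparison, including the default outcome, is not biased.

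The conclusion rests on reading presence for care as a condition of eligibility, which is how the criteria are written. The preference for round 2 rests on the assumed start of the trial period.

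**What to change.** **Main change, in Participant recruitment and informed consent.** Add treatment-interruption history (uninterrupted; interrupted, including returned after interruption) to the patient sampling characteristics. Reserve about 3–4 of the existing 10–15 patient interviews in round 2 for patients who interrupted. With four districts, that is about one per district. It leaves between 10 − 4 = 6 and 15 − 3 = 12 round 2 interviews for other patients, and the overall total stays at 40–60.

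**Optional extension, if the team also wants patients still out of care.** Widen Setting and participants and Inclusion and exclusion criteria together, to patients registered at a participating health center who began treatment during the trial period. Let health center staff make the first contact from the center's own records, so that the limit on identifiers in Data management is kept. Leave written, in-person consent as it is.

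**Cost.** The main change means slightly fewer interviews with uninterrupted patients and some extra contact effort by existing staff. The extension adds an ethics amendment, and some patients will not be reachable.
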